## Background

The HIV/AIDS epidemic in China is developing rapidly in recent years, with the number of people living with HIV increasing from 0.44 million in 2011 to 0.95 million in 2019 [1, 2]. Men who have sex with men (MSM) are the major key population of HIV/AIDS. Male homosexual transmission has become the second major HIV transmission route in China only after heterosexual transmission, which accounts for about a quarter of the new HIV/AIDS cases [2, 3]. Having unprotected anal sex is the main risk of MSM to be infected, which is also associated with interrelated risk factors, such as non-persistent sexual partners, alcohol and drug use, and co-infection of other sexually transmitted diseases (STDs) [4–10].

With the development of the Internet and the popularity of mobile devices, the ways and venues of MSM seeking sexual partners had changed dramatically. A change from seeking sexual partners through offline venues, such as gay bars, baths and parks, to online ways through Internet or mobile applications (app) is witnessed in recent years [11–13]. The rise of online dating applications (ie, Blued, Grindr) in China tremendously reduces the cost and inconvenience for MSM to seek casual sexual partners [14–16]. Some MSM who sought sexual partners through the Internet do not know each other before, not to mention each other’s HIV infection status, which brings higher risk of HIV transmissions [17, 18]. In addition, the convenience of transportation increases the risk of cross-regional HIV transmission. All of these lead to greater difficulties in HIV prevention and control among MSM who sought sexual partners through Internet, as it is always difficult to find the sexual partner again afterwards. Recent research in China showed the HIV incidence among MSM online dating apps users was about four times higher than that of nonusers (8.5 per 100 person-years vs 2.0 per 100 person-years) [19]. Therefore, MSM’s behaviors of seeking sexual partners through Internet should be paid more attention. It is important for them to know their sexual partners’ real HIV status, strengthen the awareness of health self-responsibility and give each other the opportunity to make decisions on whether to meet and have sex.

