Partner notification is a public health approach to prevent and control HIV infection among HIV high-risk subpopulations, especially MSM. It is recommended by the World Health Organization (WHO) and has been implemented in 67 countries around the world, including China [20]. Partner notification denotes that the sexual partners should take the initiative to tell each other their HIV infection statuses, especially those living with HIV/AIDS; it also encourages sexual partners to receive HIV testing [20]. Most existing methods of partner notification target to newly HIV-infected individuals’ sexual partners, for example, health workers may provide assisted HIV partner notification services on the condition that the newly HIV-infected individuals agree to, through personal telephone or address contact, e-postcards, and some website-based methods [21–23]. However, these methods aimed to offer HIV-infected individuals an opportunity to tell their sexual partners about their HIV statuses anonymously after sexual behaviors, which is a afterward remedy. Partners of the HIV-infected individuals are still at high risks. Meanwhile, some issues on the feasibility and effectiveness of these existing partner notification methods exist, including difficulties in daily implementation, low response rate, and high cost in time, human resources etc. [24, 25].

Seeing these problems, we developed a mobile health (mHealth) app for partner notification to encourage interactive queries among MSM before having sex, even before meeting. It targets not only to HIV-infected MSM, but HIV negative MSM as well. Through integrating the mHealth app to the current HIV and other STDs prevention and control methods, we set up a new and feasible public health intervention paradigm, to realize the goal of moving forward the intervention and reduce the HIV incidence among MSM.

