The second outcomes of this research include: (1) Positive seroconversion rate (incidence) of syphilis, hepatitis B, and hepatitis C. These indicators are calculated separately as the number of syphilis/hepatitis B/hepatitis C seroconversions divided by the total number of person-years. (2) HIV and related STDs transmission among social networks. Based on the partner notification information, we will construct the transmission networks of HIV and other STDs (syphilis, hepatitis B, and hepatitis C) among participants, and analyze the characteristics of these networks and factors associated with transmission of these diseases. (3) Testing adherence. This indicator is calculated as the proportion of participants whose every adjacent testing interval is no more than 3 months as recommended by China CDC. (4) Additional cost for finding per seroconversion. This indicator is calculated through the total additional cost of the integrated intervention model based on the existing HIV prevention measures provided as before divided by the total number of the HIV and STDs seroconversions. (5) Frequency of utilization for each intervention/service. This indicator is calculated through the total and average frequency of utilization for each intervention/service, such as health education, partner notification, HIV and STDs testing and so on. (6) Satisfaction of the interventions and services, measured through the follow-up questionnaires by the degree of satisfaction for participants of HIV and STDs testing service, health education, partner notification and other app’s functions. (7) Knowledge of HIV and related STDs. This indicator is measured by the baseline and follow-up questionnaires. The score of knowledge questions in the questionnaires will be used to represent participants’ level of knowledge. (8) Health self-responsibility awareness, including attitudes of HIV and STDs testing, safe sexual behaviors and partner notification. The attitudes are collected by questions in the baseline and follow-up questionnaires. (9) Sexual behaviors. They are measured through questionnaires, including questions about the number of different kinds of sexual partners, frequency of anal sex, condom use, and partner notification implementation. (10) Substance use behaviors. This indicator is measured by questionnaires about participants’ usage of methamphetamine, heroin, ecstasy, and some other sex-promoting drugs. (11) Psychological status. Self-rating anxiety scale (SAS) and Self-rating depression scale (SDS) are used to measure participants’ psychological status through questionnaires. (12) Referral rate of HIV and related STDs. This indicator is calculated as the proportion of new HIV and STDs infections who have received treatment. (Additional file 2).

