### Analysis

Descriptive analysis will be used to summarize the socio-demographic characteristics, HIV and STDs incidences, as well as knowledge, attitudes and related behaviors of total participants and different subgroups. To investigate the effects of the additional partner notification intervention, we will compare the differences of these primary and secondary outcomes in the control period and in the intervention period. As the HIV and STDs infection and most of the secondary outcomes are categorical variables, the generalized linear mixed models (GLMM) will be used for analysis. The model will include intervention status (in intervention period or not) and time as fixed effects and clusters (the districts) and individuals as random effects. The estimated effects of partner notification will be reported as risk ratio (RR) for binary outcomes and mean difference for continuous outcomes. 95% confidential intervals (CI) and *p* values will also be reported. The total and average additional costs of the intervention will be calculated to reflect the cost-effectiveness of the additional interventions, and the differences of these indicators in the control period and intervention period will be compared. Based on the connections recorded in the partner notification records of the database, social network visualization will be conducted to reflect the real connections of the participants. Social network analysis, such as calculation of degree, density, clique, degree centrality, closeness centrality, betweenness centrality, clustering coefficient, and so on, will be used to describe the characteristics of the social networks. Several transmission models of HIV and STDs will be formed to reflect the diseases transmission among MSM.

Sub-analysis will include: comparison of the effects in different age groups, different sex roles (insertive only, receptive only, both), different usage of HIV and STDs testing services (“Mailing rapid test reagent kit” only, the facility-based only, both). A sensitivity analysis will be conducted to evaluate the cluster (the district)-level effect. We will use the outcomes of each district across the follow-ups as the dependent variable, and fit a linear mixed model with the random effect of clusters (the districts).

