In this research, we create a feasible and affordable public health intervention paradigm, based on the existing HIV and STDs control methods. We integrate health education to strengthen their safety awareness and health self-responsibility, HIV and STDs testing prompting service and partner notification through app platform. To promote the convenience and privacy of HIV and STDs testing, we innovatively adopt multiple forms of testing service including the newly online HIV self-testing method “Mailing rapid test reagent kit” and the facility-based service. It can give participants more choices and may improve the adherence of the research. In this research, the SW-CRCT design is used for ethical and logistical concerns, which can minimize bias and make sure all participants receive the partner notification intervention. We expect our partner notification intervention can reduce the incidence of HIV and other related STDs, and it is cost-effective to be widely popularized in HIV and STDs control activities. It may also improve MSM’s knowledge, health self-responsibility awareness of HIV and STDs prevention, and testing adherence, as well as to reduce high risk behaviors. Based on the partner notification records we collect through the app, an innovative social network analysis will be conducted. The networks formed by the real partner notification connections are more objective and comprehensive than the connections found by traditional observational or cohort studies. The characteristics of the social networks can provide more guidance for HIV and STDs control among MSM.

One limitation of this research is that even though the interventions based on Internet and mobile phone app can be easily accepted by youth participants, some elderly people might feel it difficult to use. But it is worth noting that recent researches have showed that the age of recruited MSM is mainly 25 to 40 years old.

Our research is the first study to conduct Internet- and app-based integrated partner notification intervention in a large simple size, and will generate important research and policy implications for HIV and STDs control among MSM.

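### The transmission networks rest on partner-status requests, which are meant to precede the decision to meet, and no described step confirms that a logged pair had sex

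*Protocol article*

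**What the plan says.** Under Outcomes, secondary outcome (2) of the protocol article reads: "Based on the partner notification information, we will construct the transmission networks of HIV and other STDs (syphilis, hepatitis B, and hepatitis C) among participants". The characteristics of these networks, and what is associated with transmission, are then to be analyzed.

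The Analysis section takes its connections from the partner notification records in the database and states that "social network visualization will be conducted to reflect the real connections of the participants". Degree, density, several centrality measures and the clustering coefficient follow. The paragraph ends: "Several transmission models of HIV and STDs will be formed to reflect the diseases transmission among MSM". The Discussion adds: "The networks formed by the real partner notification connections are more objective and comprehensive", the comparison being with links found in traditional observational or cohort studies.

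On what a request is for, the Background says the app was developed to "encourage interactive queries among MSM before having sex, even before meeting", and that men who find partners online should "give each other the opportunity to make decisions on whether to meet and have sex". Intervention implementation and the Discussion likewise place the request before the men meet. The Partner notification module section describes the record itself: one user enters another's phone number, and the other agrees or refuses.

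**The concern.** A network meant to show how infection moves needs links along which infection could have moved. For these diseases in this setting, that means at least sexual contact. The recorded event is a request for information, made while contact is still undecided. When a positive result is disclosed and the men then do not meet, the intervention has done what it was built to do, yet the log still holds a link between them.

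At stake is what secondary outcome (2) can conclude. A man who checks many prospective partners gains a high degree because he is careful, and nothing in the described record separates him from a man with many sexual contacts. The Discussion offers the network characteristics as guidance for HIV and STD control, so a reader could act on a measure of requesting as though it measured exposure.

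**Working it through.** The article gives no figure on this point to reproduce. The check sets its statements side by side, then illustrates how the error would behave.

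**What the text establishes**

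1. Source of links: partner notification records (Outcomes, secondary outcome 2; Analysis). No other source of links is named.
2. Content of a record: a request by phone number, then agreement or refusal (Partner notification module). No later entry on whether sex took place is described. Whether a refused request counts as a link is not stated.
3. Intended timing: before the men decide to meet (Background; Intervention implementation; Discussion).
4. Response to the result: the app issues prompts and warnings intended to protect the requester (Prompt and warning module).
5. Who is in the network: men HIV-positive at their first test are left out of the other outcomes but kept for the social network outcomes (Eligibility and exclusion criteria). Links to men known to be positive are therefore included by design.
6. Other sexual data: the questionnaire topics listed under Outcomes are numbers of partners of different kinds, frequency of anal sex, condom use and partner notification practice. They are described per participant, not per requested pair, and neither Outcomes nor Analysis uses them to build the network.

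From 1 to 3, a pair who avoided contact and a pair who had sex leave the same kind of link. From 4 and 5, links on which a positive result was disclosed are the ones where avoidance is most to be expected.

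**Illustration 1: number of links.** Let q be the share of logged pairs who never had sex. This is an assumption; the article gives none. Of L logged links, (1 − q)L join men who had sex, so the log overstates the links by L / [(1 − q)L] = 1/(1 − q).

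| q | 1/(1 − q) |
|---|---|
| 0.10 | 1.11 |
| 0.25 | 1.33 |
| 0.50 | 2.0 |
| 0.75 | 4.0 |

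Over the same set of men, mean degree and density are proportional to the number of links and are overstated by the same factor. This concerns logged pairs only. Sex without a request, or with men outside the app, leaves no link and is an error in the other direction.

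**Illustration 2: which links.** Let π be the share of logged links that disclosed a positive result, a the share of those pairs who avoided sex, and b the share of all other pairs who did not have sex. All three are assumed. Among logged pairs who did have sex, positive-disclosure pairs make up

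π(1 − a) / [π(1 − a) + (1 − π)(1 − b)].

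With b = 0.20:

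| π (share in the log) | a | Calculation | Share among sexual links |
|---|---|---|---|
| 0.10 | 0.50 | 0.050 / (0.050 + 0.720) | 6.5% |
| 0.10 | 0.90 | 0.010 / (0.010 + 0.720) | 1.4% |
| 0.05 | 0.50 | 0.025 / (0.025 + 0.760) | 3.2% |
| 0.05 | 0.90 | 0.005 / (0.005 + 0.760) | 0.65% |

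Whenever a exceeds b, the log over-represents positive-disclosure pairs, and the distortion grows as disclosure changes behavior more. If a equals b, the share is unchanged. The selectivity therefore depends on disclosure having an effect, which is what the trial hypothesizes.

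**The case against.** The strongest reply is that the article nowhere says each request is a transmission event. Drawing the network, describing it and modelling transmission are listed as separate steps, and the models are unspecified. Data management links test results with dates, questionnaires and notification records by a unique ID. A model that requires a seroconversion would not assign a transmission to a man who avoided sex and stayed negative. Link definitions and model details are commonly left to the full protocol or analysis plan. This stands: a reader might infer that avoided pairs will be drawn as transmission events, or that the request log is the only input, and the text supports neither.

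The questionnaires are also not shown, and the topics are introduced as inclusions. One can say only that no pair-level confirmation of sex is described, not that none exists.

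Pre-meeting use is an aim and not a rule. The app lets a man query a regular partner, so some links are sexual contacts. That is true, but the record as described cannot tell the two kinds apart.

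A reader might go further and conclude that serodiscordant links in general are mostly pairs without contact. That does not follow. The argument covers links where a positive result was disclosed. A positive man may query a negative one, a request may be refused, and a man infected since his last test may show a negative result. In that last case sex may well follow.

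What does not fall is the stated basis. The article itself names partner notification information as the foundation of the transmission networks, and says the drawing reflects real connections. That is a statement in the text, not an omitted detail.

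**Conclusion.** The point holds as a mismatch between what is recorded and what it is said to represent. Followed as written, contacts that were considered and then avoided enter the network from which transmission is to be inferred, and they look the same as exposures. The problem is probably largest where a positive result was disclosed.

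Its size cannot be given. The factors of 1.11 to 4.0, and the falls from 10% to between 6.5% and 1.4% and from 5% to between 3.2% and 0.65%, rest wholly on assumed inputs. They show direction and behavior, not an estimate. Nor can it be said that associations with transmission would change sign: no model or covariates are stated, so that would be conjecture.

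The consequence is confined to secondary outcome (2), one of twelve, and to the transmission models. The primary HIV incidence analysis does not use the network. The correction is worth making because the outcome is pre-specified and the missing information would be hard to recover reliably afterwards.

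**What to change.** 1. In Outcomes and Analysis, call it a partner-status request network. Report degree, density and centrality as describing requests, not sexual or transmission contacts.
2. Remove or qualify the claim in Analysis that the drawing reflects real connections, and the claim in the Discussion that these links are more objective and comprehensive than those of traditional studies.
3. Add one pair-level yes/no item, with date, asking whether sex with that man took place. It can sit in the app or in the existing follow-up questionnaire.
4. Use only confirmed pairs in the transmission models and in the analysis of what is associated with transmission. Keep confirmed contacts of men who did not seroconvert as the comparison group. Apply the window from last negative to first positive test only when assigning a possible source to a man who seroconverted. Applied to every link, it would remove the non-transmitting contacts and leave nothing to compare against.
5. If the item is not added, report the request network descriptively and draw no transmission inference from it.

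The cost is revised wording and one short item, with no extra participants or visits. Trial status says recruitment had not begun when the article was written, so the item could be in place from the start. The downsides are self-report on a sensitive question about an identified partner, some non-response, and a smaller confirmed-contact network.

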## Discussion

One important reason that HIV keeps increasing among MSM in China is that most MSM seeking causal sexual partners through online dating platforms (such as Blued and Zank), as it results in much more risk sexual behaviors for HIV and other STDs transmission [30, 31]. Partner notification of HIV and STDs infection statuses before they decide to meet and have sex can be an important and feasible method to reduce the HIV and STDs transmission among sexually active MSM. China’s Internet penetration rate has reached 61.2% by June 2019, and 99.1% of Internet users use mobile phones to surf the Internet [32]. The intervention tools based on the WeChat-the most popular mobile phone social software [33], and a website-based app enable the method more acceptable, convenient and intimate for MSM. It may lead to better effects compared with the existing partner notification methods provided by health workers individually or through email cards. An observational study using the previous version of this app has shown a potential positive effect of the app-based partner notification intervention in reducing HIV infection among MSM [29]. An encouraging finding was that the longer the app was used, the lower the HIV incidence (> 5 months vs ≤ 5 months: 2.22 per 100 person-years vs 6.99 per 100 person-years; risk ratio 0.32, 95% CI 0.12–0.87), and the app has also been proved to be user-friendly and could be accepted and widely used by MSM [29]. However, the blank control without receiving the partner notification intervention was lacking in the observational study. Meanwhile, the observation period was only 1 year and the sample size was small, so the effectiveness of the intervention needs to be further evaluated by this trial.

In this research, we create a feasible and affordable public health intervention paradigm, based on the existing HIV and STDs control methods. We integrate health education to strengthen their safety awareness and health self-responsibility, HIV and STDs testing prompting service and partner notification through app platform. To promote the convenience and privacy of HIV and STDs testing, we innovatively adopt multiple forms of testing service including the newly online HIV self-testing method “Mailing rapid test reagent kit” and the facility-based service. It can give participants more choices and may improve the adherence of the research. In this research, the SW-CRCT design is used for ethical and logistical concerns, which can minimize bias and make sure all participants receive the partner notification intervention. We expect our partner notification intervention can reduce the incidence of HIV and other related STDs, and it is cost-effective to be widely popularized in HIV and STDs control activities. It may also improve MSM’s knowledge, health self-responsibility awareness of HIV and STDs prevention, and testing adherence, as well as to reduce high risk behaviors. Based on the partner notification records we collect through the app, an innovative social network analysis will be conducted. The networks formed by the real partner notification connections are more objective and comprehensive than the connections found by traditional observational or cohort studies. The characteristics of the social networks can provide more guidance for HIV and STDs control among MSM.

One limitation of this research is that even though the interventions based on Internet and mobile phone app can be easily accepted by youth participants, some elderly people might feel it difficult to use. But it is worth noting that recent researches have showed that the age of recruited MSM is mainly 25 to 40 years old.

Our research is the first study to conduct Internet- and app-based integrated partner notification intervention in a large simple size, and will generate important research and policy implications for HIV and STDs control among MSM.

